## Abstract

**Background:**

Frailty is a state of low physiological reserve and multi-systemic dysregulation that leads to susceptibility to external stressors; it is associated with adverse outcomes. North American data suggest that haemodialysis recipients are more likely to be frail than the general population, although data on UK cohorts are lacking. Furthermore, with a multitude of assessment tools, it is difficult for the clinician to ascertain which is most suitable for this population. The FITNESS Study aims to measure the prevalence and outcomes associated with frailty in a large UK haemodialysis cohort to determine the optimum frailty tool as defined by predictive value for mortality/hospitalisation and to conduct a feasibility study exploring a multi-disciplinary clinical intervention to improve frailty among haemodialysis recipients.

**Methods/design:**

The study will follow a cohort multiple randomised controlled trial design; the initial cohort study will identify participants to be invited into a subsequent open-label randomised controlled trial. Eligible patients will be identified and recruited from their usual haemodialysis session. They will be invited to complete tasks and questionnaires collecting data on sarcopenia, immunosenescence, mood, cognition, disability, and comorbidity. Fifty pre-frail participants with suitable English proficiency will be randomly selected from this cohort to participate in the randomised controlled trial phase of the study. Further stratified randomisation will occur to assign these 50 participants to active or passive groups. The active group will receive a psychologically supported, patient-centred, multi-disciplinary intervention into frailty, in what we believe to be a first within this patient group. The control group will receive usual haemodialysis standard of care. All participants will be followed up using electronic patient records for outcomes to include hospitalisation and mortality. Primary outcomes for this phase of the study will be feasibility and tolerability of the clinical intervention study.

**Discussion:**

The study will collect data on multiple aspects of frailty allowing for a rich dataset for detailed analysis. We believe this will be the first study to explore a psychologically supported, patient-centred intervention in this patient group.

**Trial registration:**

Clinicaltrials.gov, NCT03071107. Registered on 6 March 2017.

**Electronic supplementary material:**

The online version of this article (10.1186/s13063-018-2842-x) contains supplementary material, which is available to authorized users.

## Background

Frailty is a state of low physiological reserve and multi-systemic dysregulation that leaves the individual susceptible to external stressors [1]. Sarcopenia, an age-related, involuntary loss of skeletal muscle mass and strength and/or function is often seen as part of the frailty syndrome [2, 3]. Immunosenescence is another component of frailty, characterised by age-related deterioration in immune function, and is thought to be modifiable through exercise [4]. Frailty is prevalent among patients receiving haemodialysis, ranging between 30% to as high as 78% dependent upon the diagnostic tool used, and is associated with significant adverse outcomes such as falls, hospitalisation, mortality, and loss of functional independence [5–17]. These studies were conducted in North American cohorts, primarily using the Fried Frailty Phenotype, and to date we have no information regarding the prevalence or outcomes associated with frailty in a UK cohort. Dialysis outcomes differ significantly between these populations [18], limiting the generalisability of US data to UK cohorts. Whilst there are a range of validated subjective and objective measurements for frailty, it is unclear which has the most utility to guide clinical practice.

While frailty is not a fixed physiological state, there is currently no evidence to support any intervention targeted to improve frailty within patients receiving haemodialysis. In the general elderly population, there is some evidence of the utility of a multi-disciplinary approach to intervene on frailty. For example, the FIT study utilised a multi-factorial inter-disciplinary intervention which reduced frailty among older people by 14.7% at 12 months [19]; however, there were no other outcomes measured, such as quality of life, mortality, or hospital admissions. The majority of frailty intervention studies performed in both general and dialysis populations do not use validated measures of frailty for either inclusion criteria or outcome measures, but show that functional outcomes (i.e. disability) can be improved with exercise [20–22]. For those patients proceeding to kidney transplantation, frailty at the time of transplantation has been associated with poorer post-transplant outcomes [23–26], although there have not been any published attempts at “prehab” in prospective transplant recipients. Therefore, whether such a strategy would lead to more haemodialysis patients being deemed suitable to benefit from transplantation remains to be seen.

We speculate that patient behaviours can be modified to impact upon frailty. To the best of our knowledge, there have not been any published attempts to intervene upon frailty using behavioural change. Meta-analysis and meta-regression have shown that behavioural change techniques (BCTs) congruent with control theory [27] are significantly more effective than those that are not [28–30]. These include node-link mapping (NLM), which incorporates visual representations of behavioural change, alongside potential aids and barriers to this change with strategies to overcome these [31]. NLM is a technique already successfully used in addiction psychiatry [32]. Social behaviour and network therapy (SBNT) seeks to identify the level of social support for an individual, and aims to include significant supportive others in setting and monitoring goals, and has been successfully used in alcohol abstinence after liver transplantation [33].

It is speculated that long-term changes in behaviour and activity are likely to be required to impact upon frailty and, as such, BCTs may have a role to play in frailty interventions.

## Aims

This study aims to: 1) measure prevalence and outcomes associated with frailty in a large UK haemodialysis cohort; 2) determine the optimum frailty assessment tool for UK patients receiving haemodialysis, as defined by predictive value for mortality/hospitalisation; and 3) conduct a feasibility study exploring a multi-disciplinary clinical intervention to improve frailty status among patients receiving haemodialysis

## Methods/design

This is a prospective, single centre, open-label, cohort multiple randomised controlled trial (cm-RCT) [34] which will be split into two elements. Work package 1 is a cohort study of prevalent haemodialysis patients which aims to identify the prevalence of frailty among this population and outcomes associated with frailty such as mortality, hospitalisation, and quality of life. Patients from work package 1 who are identified as “pre-frail”, as defined by the Frailty Index, will then be invited to participate in work package 2 which will compare the effect of active lifestyle intervention versus current standard of care upon frailty measurements and outcomes. All haemodialysis patients who meet the inclusion/exclusion criteria will be invited to participate in work package 1. As part of the cm-RCT design, eligible patients will be selected for invitation to participate in work package 2 according to a stratified randomisation module. Invited participants will be randomised into active or passive intervention groups. The duration of the clinical intervention in work package 2 will be 6 months, with electronic data-linkage follow-up for 5 years after study participation to allow for continued capture of outcome measures.

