#### Work package 2: inclusion criteria

The inclusion criteria for work package 2 are: 1) aged 18 years and over; 2) received regular haemodialysis of at least 3 months duration; 3) able to provide informed consent; 4) a participant in work package 1; 5) identified as pre-frail in work package 1; and 6) suitable English proficiency, i.e. an ability to understand a medical consultation in English.

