#### Passive control group

This group will receive their usual standard of care from their treating dialysis centre, including usual dietitian input. However, there will be no psychosocial intervention or focused exercise and dietary monitoring programme. Follow-up will be at routine clinic visits only, where lifestyle modification advice will be reinforced as per usual clinical practise. Physiotherapy may be offered to these patients as per standard referral guidelines but will not have the psychosocial underpinning of the intervention group.

Both groups will undergo a repeat frailty testing during the mid-point (3 months ± 2 weeks) and the end of study intervention (6 months ± 2 weeks) (see Figs. 1 and 2). The aim is to assess if there is any change in frailty status which will provide data to underpin a power calculation for a subsequent large-scale study. Additional pre-specified secondary outcomes will be collected as highlighted below in the protocol. Participants will also be invited to complete a series of questionnaires to ascertain the tolerability and suitability of the intervention trial, and to guide the delivery of the trial on a larger scale.

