#### Secondary endpoints

Secondary endpoints include: 1) refinement of the multi-disciplinary intervention based upon views from participants and stakeholders (from post-study questionnaires); 2) change in frailty status (based on Fried Frailty Phenotype, Clinical Frailty Scale); 3) difference in clinical and biochemical outcomes; 4) quality of life score (EQ-5D-3 L); 5) receipt of kidney transplant; 6) vascular access failure; and 7) long-term clinical outcomes (death, cardiac events, hospitalisation) to University Hospital Birmingham electronic patient records and Hospital Episode Statistics

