## Discussion

Frailty has been linked with adverse outcomes in North American haemodialysis cohorts [5–12, 17, 39, 40], but these data are not transferrable to UK patients since US dialysis populations have adverse outcomes compared with UK populations [18]. There is no agreement over the best frailty tool to assess patients, both within the general population and within haemodialysis cohorts. The Fried Frailty Phenotype [41] and Rockwood Frailty Index [42] are the most commonly cited instruments in geriatric and renal-specific literature, with the Clinical Frailty Scale also featuring in haemodialysis cohorts [12]. The Edmonton Frail Scale is recommended by the British Geriatric Society, but has yet to be validated in patients receiving haemodialysis [43]. We expect each of these instruments to show association with negative outcomes, but it is not yet known which of these provides the best predictive value in patients receiving haemodialysis. The cohort analysis embedded within this study will therefore seek to address this by comparing frailty instruments for their association with negative outcomes, whilst also addressing renal-specific outcomes such as transplantation or dialysis access failure. These data will allow renal practitioners to better understand which frailty tool is optimal for their population.

Multi-disciplinary intervention into frailty has shown promise [19], although a systematic review and meta-analysis was limited by the lack of validated measures of frailty as inclusion criteria and outcome measures in the published studies to date [22]. To our knowledge, there are no published data regarding frailty interventions within the UK haemodialysis population, although a US study showed self-reported disability could be reduced by such an intervention [20].

There is an urgent need for the development of interventions capable of enacting long-term change within patient groups. Our experience in Birmingham suggests that BCTs can modify behaviour with the potential to change clinical outcomes [33, 44]. Therefore, a patient-centred, frailty-specific BCT intervention may be beneficial for frail patients receiving haemodialysis and may improve clinical and patient-reported outcomes.

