Work package 2 is an unblinded, randomised controlled study using a psychologically supported multi-disciplinary intervention into frailty compared with a control group which receives standard care. This will be used as a basis for exploring whether a large scale, multi-centre trial is feasible and warranted, while also providing data upon effect sizes to allow subsequent power calculation for such a study. We chose the “pre-frail” group as the focus of this intervention, firstly because they arguably have the most to gain—not progressing to frailty—and, secondly, because pre-frailty represents a much less heterogeneous group than frailty, the latter of which would include essentially functionally independent individuals with a few accumulated deficits along with bed-bound individuals and those approaching end-of-life. The pre-frail group therefore have an easily definable set of characteristics and have the ability to participate in, and benefit from, the proposed interventions.

One of the principle strengths of the study design is the breadth of data being collected. Researchers will collect data on multiple aspects of frailty from consenting patients to include aspects of sarcopenia (muscle mass, quality, and function), immunosenescence, functional status/disability, mood, cognitive status, and medical history. This rich dataset will allow detailed analysis of the heterogeneity or otherwise of frailty within the cohort. As work package 1 is a single time-point analysis with electronic follow-up thereafter, dropout should be minimal and large numbers of patients could be recruited to allow such detailed analysis to have real meaning to clinicians. Another strength lies in the cm-RCT design, whereby stratified random sampling will identify trial participants from consenting eligible cohort study participants. This approach has several benefits, including amelioration of potential attrition bias in the control group, long-term data follow-up for a large comparator group, and increased power for the study [34].

A weakness of the study is the single time-point assessment in work package 1, as frailty is known to change over time [45–47]. Nevertheless, objective frailty measurements still hold prognostic value [48].

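### Work package 2 selects pre-frail patients on the Frailty Index, but its change-in-frailty endpoint names only the Fried Phenotype and the Clinical Frailty Scale

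*Protocol article*

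**What the plan says.** Entry. The Methods/design section of the protocol article says that patients classed as pre-frail, "as defined by the Frailty Index, will then be invited to participate in work package 2". The work package 2 inclusion criteria then require a patient to be "identified as pre-frail in work package 1" and name no other instrument.

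Outcome. The second secondary endpoint is "change in frailty status (based on Fried Frailty Phenotype, Clinical Frailty Scale". The Frailty Index is not in that list.

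Timing and use. Under Passive control group: "Both groups will undergo a repeat frailty testing during the mid-point (3 months ± 2 weeks) and the end of study intervention". No tool is named there. The purpose is to look for "any change in frailty status which will provide data to underpin a power calculation for a subsequent large-scale study".

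Rationale. The Discussion explains that pre-frail patients were chosen because "they arguably have the most to gain—not progressing to frailty", and because they form a more uniform group than frail patients.

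The tools are distinct. The Discussion says: "The Fried Frailty Phenotype [41] and Rockwood Frailty Index [42] are the most commonly cited instruments". It lists the Clinical Frailty Scale as a further tool, so these are not different names for one measure.

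**The concern.** Pre-frail is a category on a particular scale. Choosing pre-frail patients because they can be kept from becoming frail, and because they are alike, works on the scale that assigned the category. It need not carry over to another scale. Among patients who are pre-frail on the Index, some may already be frail on Fried or the Clinical Frailty Scale, and some may be robust.

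What is at stake is the planning information. The frailty-change data are meant to help size a larger trial. If that trial also recruits on the Index, no listed endpoint here gives a rate of progression on the Index. The rates on the other two scales would come from a group that did not all start pre-frail on them.

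**Working it through.** The plan has no figure to reproduce on this point. Work package 2 has no power calculation, and the sample sizes in the Statistics section (602 and 150) concern work package 1 only. The check is a comparison of the text, followed by an illustration.

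**Text side by side**

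- Entry instrument (Methods/design): Frailty Index.
- Change instruments (Secondary endpoints): Fried Frailty Phenotype and Clinical Frailty Scale.
- Overlap between the two lists: none.
- Repeat testing at 3 and 6 months (Passive control group): instruments not named.
- Target transition (Discussion): pre-frail to frail.
- Use of the change data (Passive control group, Statistics, Discussion): sizing a later trial.

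**What category change on Fried would contain**

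Let P, F and R be the shares of participants who are pre-frail, frail and robust on Fried at baseline, with P + F + R = 1. The proportion frail on Fried at 6 months is

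P × (rate pre-frail to frail) + F × (rate staying frail) + R × (rate robust to frail).

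Only the first rate is the transition that motivates the study. If everyone were pre-frail on Fried at baseline, P would be 1 and the other terms would vanish. Selection on the Index does not ensure this. The same reasoning applies to the Clinical Frailty Scale.

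**Illustration of size**

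Inputs from the document: 50 participants, 25 per arm. P is not given, so I assume 0.4 to 0.8, a range with no anchor in the document.

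- Pre-frail on Fried at baseline: 50 × 0.4 = 20, to 50 × 0.8 = 40.
- Per arm: 25 × 0.4 = 10, to 25 × 0.8 = 20.
- Starting in another Fried category: 50 − 40 = 10, to 50 − 20 = 30.
- Pre-frail-to-frail moves on Fried, counted over all participants: P × rate, which is 40% to 80% of the rate among those who could make that move.

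A restricted analysis removes this last dilution, but it still estimates progression on Fried and not on the Index.

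**The case against.** The strongest reply is that the gap is narrower than it looks and falls where it does least harm. Most of this stands.

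- A reader might infer that progression is never measured on the Index. The document does not establish that. The repeat frailty testing names no tool, and the SPIRIT figure is not available in the text reviewed, so the Index may well be repeated. What the text shows is that the Index is not listed among the instruments for the change endpoint.
- A reader might infer that patients in another Fried category cannot contribute. They are blocked in one direction only: someone frail at baseline can improve and someone robust can decline. The endpoint is change, and the third aim speaks of improving frailty status.
- A reader might infer that the endpoint cannot show whether pre-frail patients were kept from frailty. Those who are pre-frail on Fried at baseline could show exactly that, on Fried.
- The Background gives a prevalence range of 30% to 78% depending on the tool. That range runs across published studies, mostly using Fried. It makes disagreement between tools plausible but does not measure agreement within patients.
- Change in frailty is one of seven secondary endpoints in a feasibility study. The primary endpoint (recruitment, loss to follow-up, withdrawal) does not depend on the instrument.
- Finding the best tool is itself an aim of work package 1, so making the Index the lead measure would be a preference and not a correction.

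The reply does not remove the mismatch. The article names the instruments for entry and for change, and the two lists do not meet. This is something the document fixes, not a detail left to an analysis plan.

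**Conclusion.** The mismatch is stated in the text and is worth correcting. Category change on Fried and the Clinical Frailty Scale mixes baseline states. It does not directly estimate the pre-frail-to-frail transition for a group defined on the Index.

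The size is unknown. The figure of 20 to 40 out of 50 rests wholly on the assumed 40% to 80% agreement with Fried, and no comparable range is offered for the Clinical Frailty Scale. The conclusion does not need the range. It needs only that the three tools can classify the same patient differently, which the protocol's plan to compare them presupposes.

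The consequence is confined to a secondary endpoint and to the effect sizes carried into the next trial. This is a cheap improvement, not a must-fix.

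**What to change.** 1. In Secondary endpoints, add the Frailty Index, as score and category, to the instruments for change in frailty status.
2. Under Passive control group, name the tools repeated at 3 and 6 months and include the Index.
3. Compare the arms on each instrument's score, adjusted for its own baseline value.
4. Report pre-frail-to-frail transitions for each instrument among those pre-frail on that instrument at baseline, with the denominator shown.

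None of the three tools has to be ranked first. Defining entry on an instrument that the endpoint already uses would also remove the mismatch, but it would change who is recruited.

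The cost is a little extra questionnaire work and record review at visits already scheduled, and smaller denominators for transitions on Fried and the Clinical Frailty Scale. The decision is needed before follow-up testing begins, because Index items that are not collected at 3 and 6 months cannot all be recovered later.

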### Study setting

Patients will be recruited from a single nephrology centre located in Birmingham, UK. The centre consists of one in-hospital dialysis unit and 10 private-provider satellite units distributed around the region, and provides haemodialysis to 1000 patients. It is planned to recruit at least 602 patients from this population to work package 1 with 50 patients recruited to work package 2. Birmingham and the West Midlands is a diverse, multi-cultural population and, as such, we will aim to recruit proportionate numbers of black, Asian and minority ethnic (BAME) participants to the study to accurately represent the community our hospital serves.

### Inclusion and exclusion criteria

#### Work package 1: inclusion criteria

The inclusion criteria for work package 1 are: 1) aged 18 years and over; 2) received regular haemodialysis of at least 3 months duration; and 3) able to provide informed consent.

#### Work package 1: exclusion criteria

The work package 1 exclusion criterion is having received inpatient care within 4 weeks of recruitment (unless for vascular access).

#### Work package 2: inclusion criteria

The inclusion criteria for work package 2 are: 1) aged 18 years and over; 2) received regular haemodialysis of at least 3 months duration; 3) able to provide informed consent; 4) a participant in work package 1; 5) identified as pre-frail in work package 1; and 6) suitable English proficiency, i.e. an ability to understand a medical consultation in English.

